# Promoting respectful maternity care for adolescents in Ghana: a quasi-experimental study protocol

**DOI:** 10.1186/s12978-020-00977-w

**Published:** 2020-08-24

**Keywords:** Intra-partum mistreatment, Maternal mortality, Adolescent sexual reproductive health and rights, Ghana

## Abstract

**Background:**

Intra-partum mistreatment by healthcare providers remains a global public health and human rights challenge. Adolescents, who are typically younger, poorer and less educated have been found to be disproportionately exposed to intra-partum mistreatment. In Ghana, maternal mortality remains a leading cause of death among adolescent females, despite increasing patronage of skilled birth attendance in health facilities. In response to the the World Health Organisation Human Reproduction Programme (WHO-HRP) recommendations to address mistreatment with Respectful Maternity Care (RMC), this study aims to generate evidence on promoting respectful treatment of adolescents using an intervention that trains health providers on the concept of mistreatment, their professional roles in RMC and the rights of adolescents to RMC.

**Methods:**

This study will employ a pre-test post-test quasi-experimental design. At pre-test and post-test, quantitative surveys will be conducted among adolescents who deliver at health facilities about their labour experience with mistreatment and RMC. A total target of 392 participants will be recruited across intervention and control facilities. Qualitative interviews will also be conducted with selected adolescents and health professionals for an in-depth understanding of the phenomenon. Following the pre-test, a facility-based training module will be implemented at intervention facilities for the facility midwives. The modules will be co-facilitated by the principal investigator and key resource persons from the district health directorate Quality of Care teams. Training will cover the rights of adolescents to quality healthcare, classifications of mistreatment, RMC as a concept and the role of professionals in providing RMC. No intervention will occur in the control facilities. Descriptive statistics, logistic regressions and difference in differences analyses will be computed. Qualitative data will be transcribed and thematically analysed.

**Discussion:**

This study is designed to test the success of an intervention in promoting RMC and reducing intra-partum mistreatment towards adolescents. It is expected that the findings of this study will be beneficial in adding to the body of knowledge in improving maternal healthcare and reducing maternal mortality, especially for adolescents.

**Trial registration:**

Name of the registry: Pan African Clinical Trials Registry. PACTR202008781392078.

## Plain English summary

Mistreatment during childbirth remains a well-documented worldwide challenge, especially among poorer, younger and less educated women. In Ghana, the most vulnerable groups include adolescents, who also happen to bear a disproportionately high risk of maternal mortality. Despite the increasing rates of facility-based births which are attended to by trained obstetric professionals, maternal mortality persists as a public health challenge in Ghana and sub-Saharan Africa in general. Following landscape studies which suggest that mistreatment during delivery may be a strong predictor for poor birth outcomes, the WHO has recommended that this issue be addressed with respectful maternity care. This study, therefore, aims to determine the effectiveness of a training intervention for health providers targeted at reducing mistreatment of adolescents during childbirth. This will contribute to knowledge and inform programming and policy on improving maternal healthcare and reducing maternal mortality and morbidity, especially among adolescents.

## Background

Mistreatment suffered by women who deliver within health facilities is an extensively documented phenomenon [1–3]. The most reported forms of facility-based mistreatment which often occur in a continuum are categorized as physical abuse, non-consented care, non-confidential care, non-dignified care, discrimination based on specific patient attributes, abandonment of care, and detention in facilities [4]. Whilst intrapartum mistreatment traverses geographical boundaries and socio-economic levels, [1, 2, 5–7] certain factions of women appear to bear a markedly high burden of the phenomenon [8–10]. As a group of interest, adolescent women appear disproportionately predisposed to disrespectful treatment attributable to their young age, lower educational attainment, lower socio-economic status, lack of autonomy, as well as provider and social prejudices about their engagement in pre-marital and early sex [11–15]. Mistreatment in service provision for pregnant adolescents is problematic as it compounds the already existing burden of social and health risks [11, 16–18]. Currently, maternal mortality remains one of the leading global causes of death among adolescents, especially in sub-Saharan Africa and is considered a pressing public health challenge [19]. Approximately 11% of births worldwide occur among adolescent girls aged between 15 and 19 years old, majority of which occur in low to middle income countries [20]. In Ghana, this proportion of 14% is approximately a third higher than the global average [21, 22]. Despite the absence of nationally representative data on what proportion of maternal deaths are adolescents, research suggests adolescents may constitute a larger proportion of maternal mortality and morbidity figures since they bear a higher risk of pregnancy-related complications than their older counterparts [23]. A WHO Multi-country Survey on Maternal and Newborn Health revealed that adolescents 19 years and below were twice as likely to develop eclampsia than women over 20 years of age [24]. The same study reported a 50% higher probability of systemic infections among adolescents and a 13% higher likelihood of severe maternal outcomes as compared to women over the age of 20 years. Studies investigating efficacious strategies which may successfully alleviate this burden have identified appropriately-timed intrapartum interventions to be the most beneficial means of reducing maternal mortality and morbidity compared to antenatal and postpartum interventions [25–27]. These include promoting facility-based births and as a corollary, increasing skilled birth attendance to enable early identification and management of complications [27, 28]. Accordingly, interventions in Ghana have targeted overcoming barriers to facility access especially geographic and financial factors. Financial access has been improved by waiving antenatal care and delivery fees whilst the establishment of Community-Based Health Planning Service Compounds (CHPS-Compound) has improved provision of maternal care to the last mile within communities [29–31]. Nonetheless, the proportion of facility-based births in Ghana at 78% is currently less than the global average of 81% [22]. Additionally, the national maternal mortality rate of 308 per 1000 births is still markedly higher than the global average of 211 per 1000 births and far short of the SDG target of 70 per 1000 births [21]. Within the five years preceding the 2017 Ghana Maternal and Health Survey, only 71% of pregnant adolescents utilized facility-based deliveries [22]. This has been linked to the mistreatment parturients face during facility-based births [32, 33]. This data suggests that attempts to improve maternal mortality and morbidity may be hindered by the mistreatment of adolescents during childbirth.

Consequently, the Human Reproduction Programme of the World Health Organization (WHO-HRP), has prescribed recommendations on addressing mistreatment of women during childbirth with respectful maternity care [34]. Respectful Maternity Care (RMC) refers to the organization and management of health systems in a manner that ensures respect for women’s sexual and reproductive health and human rights [34]. Indeed, the absence of RMC has been identified as a key disincentive to accessing facility-based births; even in contexts where financial and physical access are not necessarily problematic [14, 32, 35]. Studies have also reported adverse clinical outcomes like prolonged labour, unnecessary pain, haemorrhage, mental distress and in extreme cases, death [36–39] during facility based births where RMC is not practiced. This underscores the need for RMC not only to promote uptake of facility-based deliveries, but also to improve birth outcomes and reduce complications.

Considering that the sexual reproductive health and rights (SRHR) of Ghanaian adolescents are constitutionally entrenched [40], backed by research-based policy [41] and heavily invested in by the government of Ghana and other development partners, improving the quality of maternity care for adolescents should be a national priority. Moreover, whilst studies have strongly linked mistreatment to poor outcomes, there is relatively little insight on specific interventions that successfully promote RMC for adolescents. Against this background of limited information and knowledge about adolescents’ experiences and outcomes with mistreatment during childbirth, this study seeks to characterize the experiences and outcomes of adolescents who face mistreatment during facility-based births. The study seeks to test the outcome of the proposed intervention in promoting RMC during facility-based deliveries for parturient adolescents. This study also presents an opportunity in addressing some existing gaps in knowledge and information for policy and programming for adolescent maternal health and SRHR.

### Study aim

The overall aim of the study is to determine the effectiveness of a training intervention in promoting respectful maternity care for adolescents during facility-based delivery.

### Specific objectives

The specific objectives of this study are to.
Synthesise the available evidence relating to the mistreatment and the provision of respectful maternity care for adolescents during facility-based childbirth using a systematic review approach.Estimate the prevalence of mistreatment during facility-based childbirth among adolescents.Identify the risk factors and outcomes of intra-partum mistreatment during facility-based childbirth among adolescents.Document and characterize the experiences of adolescents who suffer mistreatment during facility-based childbirth.Determine the most and least common forms of Respectful Maternity Care offered to adolescent parturients.Determine the effectiveness of an intervention in promoting respectful maternity care and increasing satisfaction with facility-based births and skilled birth attendance for parturient adolescents.

### Conceptual framework

The proposed study is diagrammatically represented in Fig. 1. The conceptual framework is theoretically based and developed from the review of existent literature on intrapartum mistreatment and RMC.

**Fig. 1 Fig1:**
[figure not shown]
Conceptual Framework

## Methods

### Study settings

The study intervention will be sited in three regions in Ghana: Eastern, Central and Greater-Accra regions. The intervention sites are public health facilities in the Lower Manya Krobo, Upper Manya Krobo district, and the Awutu-Senya East Municipality. The control sites will be in the Ada East, Shai-Osudoku and Effutu Districts. These districts have an average of 11% of their population being adolescent females [42] and reported adolescent pregnancy rates higher than the national average of 14% [22] . The intervention and control sites are selected health facilities which are matched on the type of facilities being district health centres and district hospitals. For each of the intervention sites, a senior member of the district quality of care team will be included as a resource person in the RMC trainings.

### Study design

The study is a non-equivalence pre-test post-test quasi-experimental study. Both qualitative and quantitative methods will be used in data collection.

### Quantitative study population

Study participants in the quantitative phase will be adolescent females between the ages of 10 and 19 years old who deliver at the participating facilities.

### Qualitative study population

The first group of participants in the qualitative phase of this study are adolescent females between the ages of 10 and 19 years old who deliver at the participating study sites. The second group of participants are health providers in full time employment at the study sites. Adolescents and health professionals alike will be invited to participate in the study based on the study inclusion criteria and will be enrolled based on their consent to participate. Adolescents will be invited to participate in In-Depth Interviews (IDIs) and the professionals will participate in Key Informant Interviews (KIIs).

### Inclusion criteria

Adolescents will be deemed eligible for participation if they satisfy the following criteria.
i.Between the ages of 10 and 19 years.ii.Present at any of the selected health facilities for delivery, antenatal care within their third trimester or post-natal care within two weeks of delivery.iii.Consent to participate in the study.

Eligibility criteria for health professionals are.
i.Health providers including midwives and administrators who are in full time employment at the selected health facilities.ii.Consent to participate in the study.

### Exclusion criteria

Health professionals and adolescents will be excluded based on the following criteria
i.Decline to participateii.Are physically or mentally ill or indisposediii.Did not deliver at the facilities in the study if they are adolescents or are not obstetric care providers or administrative staff of the facilities

### Sample size determination

The minimum sample size for adolescents is obtained observing the assumptions that the estimated proportion of women who encounter mistreatment during childbirth is 18% [43] and the proposed intervention may reduce this by 10 percentage points. Additionally, a 5% margin of error, a 95% significance level and 80% power are estimated.
N = estimated sample size for one arm.Za = Critical value at confidence interval of 95% (1.96).Zb = Critical value at power of 80% (0.842).d = Actual difference in proportion between control and intervention groups (0.1).P = Average of difference in proportion of both groups

$$ \mathrm{N}=2\times \frac{{\left( Z\alpha + Z\beta \right)}^2}{d^2}\times p\left(1-p\right) $$

An intra-cluster design effect of 1.11 and a non-response adjustment of 10% is factored to obtain a minimum sample size of 392.

A minimum of 10 healthcare participants and 10 adolescents will be included in qualitative Key Informant Interviews It is anticipated that the number of interviews will allow a sample size large enough to allow data saturation to understand the phenomenon of mistreatment from both provider and client perspectives.

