### Sampling procedure

Multistage, stratified and systematic sampling will be used to recruit study participants from the facilities where they attend. Using data available from the 2010 Population and Housing Census, three out of the formerly ten regions in Ghana with adolescent pregnancy rates higher than the national average (14%) were randomly selected. Subsequently, six districts were purposefully selected from these regions considering appropriateness for the intervention, available resources, and geographical non-proximity between intervention and control facilities. Facilities in the intervention and control arms of the study were matched based on the number of adolescent pregnancies delivered annually using the Ghana Health Service District Health Information Management System (GHS-DHIMS) data from 2018 as a guide.

All eligible adolescent participants who attend the participating intervention and control facilities for antenatal care in their third trimester and delivery will be invited to enrol in the study by a trained research assistant. The nature of the study and all ethical concerns will be explained to the candidate prior to their enrolment. Enrolment will be run on a cumulative bases until the minimum sample size is satisfied. Some adolescents will be purposively selected to participate in the adolescent IDIs based on their characteristics which is aimed at achieving maximum variability of participants. Each district will have a health professional who works in administrative capacity and in a caregiving capacity invited to participate in the Key Informant Interviews.

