### Data processing and statistical analysis

Both baseline and endline data will be reviewed and edited for completeness and consistency daily. The primary outcome variable of interest is defined as disrespectful intrapartum care which is measured as a response of “Yes” to any of the nine mistreatment questions. The explanatory variables of interest include socio-economic status, educational level, marital status and knowledge of health rights. Data will be collected on the KoBoCollect platform, synced onto a web server and downloaded in Ms-Excel format to the principal investigator’s computer. The data will be exported in STATA version 16 for cleaning and analyses. Descriptive statistics as well as binary and multiple logistic regressions will be computed. Additionally, Difference in Differences (DID) will be calculated to determine the net RMC training intervention effect on mistreatment and RMC. Finally, statistical significance of the RMC training intervention effect will be evaluated using adjusted prevalence ratio, adjusted odds/risk ratio at 95% confidence interval (CI) and *P*-Value of less than 0.05.

Audiotapes from qualitative interviews will be translated and transcribed verbatim into Ms-Word format in English. Themes will be identified and coded in Ms-Excel and exported into NVivo for analyses. Quotes will be narrated and cited in participant codes.

Data analysis for qualitative and quantitative data will be conducted separately. Subsequently, inferences from both qualitative and quantitative results will be jointly used to draw conclusions.

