## Discussion

This study will firstly establish the prevalence of mistreatment among parturient adolescents. Several studies worldwide have reported the prevalence of mistreatment among women in general [3, 55–58]. This proposed study, however, is among the first of its type to focus exclusively on the mistreatment of adolescents. Furthermore, the study will determine the effectiveness of an intervention in promoting RMC in Ghana and reducing mistreatment. Previous studies have employed interventions that target facility users such as holding maternity open birth days and community workshops to improve public awareness about mistreatment [6, 43]. Mediation and resolution of past incidences of mistreatment whilst preventing future events has also been managed by educating communities on their SRHR whilst providing a means of legal redress [59]. Whilst these interventions may be helpful for older women, they may not be ideal for younger adolescents as they may not possess the autonomy required to properly exercise these facilities. Some interventions have also targeted providers with evidence-based information by providing access to the World Health Organization Reproductive Health Library (RHL) [60] and promoting advocacy for birth companions [61]. A study by Abuya and colleagues in Kenya recorded a 7% reduction in mistreatment following the implementation of a multi-component intervention at the policy, facility and community levels [43]. However, there was no special focus in these studies on adolescent sub-groups and their peculiar experiences or needs. This study therefore seeks to provide insight on interventions that may better address the peculiar maternal care needs of adolescent parturients.

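### The 80% power is computed for one two-group difference, but the training effect is to be estimated by a four-cell difference-in-differences, whose power is about 24% to 62% depending on how 392 is split and on the test scale

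*Protocol article*

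**What the plan says.** Under Sample size determination, the article assumes that "the estimated proportion of women who encounter mistreatment during childbirth is 18" per cent and that "the proposed intervention may reduce this by 10 percentage points". The difference entered in the formula is "d = Actual difference in proportion between control and intervention groups (0.1", with N defined per arm. The critical values are 1.96 ("Za = Critical value at confidence interval of 95% (1.96") and 0.842 for 80% power. A design effect of 1.11 and a 10% non-response adjustment are said to lead to 392. The formula has no term for the pre-test survey.

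The Methods part of the abstract gives the scope: "A total target of 392 participants will be recruited across intervention and control facilities". It does not say whether that covers one survey wave or both. Under Sampling procedure, "Enrolment will be run on a cumulative bases until the minimum sample size is satisfied".

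Under Data processing and statistical analysis, "Difference in Differences (DID) will be calculated to determine the net RMC training intervention effect on mistreatment and RMC". Table 1 (objective 6) repeats the comparison of arms at baseline and at endline. The Limitations section relies on DID to deal with differences between sites that were not randomised. The same analysis section says that significance will be judged on adjusted prevalence, odds or risk ratios at P below 0.05.

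**The concern.** The power statement and the effect analysis concern different contrasts. The formula gives the variance of one difference between two independent proportions. A DID is a difference between two such differences. Each wave surveys adolescents who have recently delivered, interviewed within two weeks of delivery, so the pre-test and post-test women are different people. There is no within-person correlation to offset the extra variance, and the variances of all four cells add.

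The study aim is the effectiveness of the training, and the article itself says that the sites may differ at baseline. The simple endline comparison, to which 80% applies, is therefore the one that the article treats as open to confounding. The DID that is meant to answer the aim has much lower power. If the training worked exactly as assumed, a non-significant result would still be quite likely, and under most readings more likely than not.

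**Working it through.** **Inputs.** From Sample size determination: 18% untreated, 8% treated, d = 0.10, z-values 1.96 and 0.842, design effect 1.11, non-response 10%. From the abstract: 392 in total across arms. My assumptions: equal cells, and 18% in the three cells without training (both baseline cells and the control endline cell).

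**Step 1: the plan's own figure.** Taking p as the mean of 0.18 and 0.08, which is 0.13:

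N = 2 × (1.96 + 0.842)² / 0.10² × 0.13 × 0.87 = 2 × 7.851 / 0.01 × 0.1131 = 177.6 per arm, or 355 for two arms.

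With both adjustments the total is 355.2 × 1.11 × 1.1 = 434, or 355.2 × 1.11 / 0.9 = 438, and not 392. One adjustment alone comes close: 2 × (178 × 1.1, rounded up to 196) = 392, and 355.2 × 1.11 = 394. So 392 does not follow from the stated steps, which is a separate point. What matters here is that it has the size of a two-arm total at one time point. A single endline comparison of 196 with 196 has 84% power with no losses, 80% after one adjustment and 76% after both.

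**Step 2: variance of the DID (risk-difference scale).**

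Var = (3 × 0.18 × 0.82 + 0.08 × 0.92) / n = (0.4428 + 0.0736) / n = 0.5164 / n, with n women per cell.

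The two-group difference has (0.1476 + 0.0736) / n = 0.2212 / n, so the DID variance is 0.5164 / 0.2212 = 2.3 times as large for the same cell size.

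**Step 3: power for 10 points**, Φ(0.10 / SE − 1.96).

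- 392 over both waves, n = 392 / 4 = 98: SE = √(0.5164 / 98) = 0.0726; Φ(1.378 − 1.96) = 28%. After both adjustments the effective n is 98 × 0.9 / 1.11 = 79.5, and power is 24%.
- 392 per wave, n = 392 / 2 = 196: SE = 0.0513; Φ(1.948 − 1.96) = 50%. After both adjustments the effective n is 158.9, and power is 42%.

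**Step 4: the ratio scales named in the analysis section.** For the interaction of arm and period:

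- Log odds: effect ln(0.18/0.82) − ln(0.08/0.92) = 0.926; variance [3/(0.18 × 0.82) + 1/(0.08 × 0.92)] / n = 33.91 / n.
- Log prevalence ratio: effect ln(0.18/0.08) = 0.811; variance (3 × 0.82/0.18 + 0.92/0.08) / n = 25.17 / n.

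| Cell size | Risk difference | Odds ratio | Prevalence ratio |
|---|---|---|---|
| 98, no losses | 28% | 35% | 36% |
| 98, both adjustments | 24% | 29% | 30% |
| 196, no losses | 50% | 61% | 62% |
| 196, both adjustments | 42% | 52% | 53% |

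**Step 5: what could be detected at 80% (risk-difference scale).** At 98 per cell, even complete elimination (18% to 0) gives SE = √(3 × 0.1476 / 98) = 0.0672 and Φ(0.18 / 0.0672 − 1.96) = 76%, so no reduction from 18% reaches 80%. At 196 per cell, with the treated-cell variance updated as the effect grows, the detectable reduction is 13.9 points with no losses and about 15 after both adjustments.

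**Step 6: cell size for 80% at 10 points (risk-difference scale).** n = 7.851 × 0.5164 / 0.01 = 405 completed interviews per cell, or 405 × 1.11 = 450 with the design effect.

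**The case against.** The strongest objection is that the size of the shortfall depends on choices that the article leaves open. The formula yields a two-arm total at one time point, so reading 392 as per wave is at least as natural as reading it over both waves, and the lowest figures all rest on the second reading. The test may be on a ratio scale, where power is higher. The 1.11 design effect may also be too harsh for a DID in the same facilities, because facility differences that are constant over time cancel; with non-response alone the risk-difference low ends are 26% and 46%. All of this stands, and it is why the result is a range. None of it restores 80%. Only 392 per arm per wave would come close (70–79% on the risk difference, 81–89% on the ratio scales), and the abstract's wording of a total across both kinds of facility excludes that.

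A reader might also infer that nothing keeps the four cells balanced. That goes too far: facilities are matched on annual adolescent deliveries, N is defined per arm, and each wave has a window of about three months. These push towards similar cells, but they are not targets per cell, and the only stated stopping rule is cumulative.

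Finally, the Discussion says that the study from which the 18% is taken "recorded a 7% reduction in mistreatment following the implementation of a multi-component intervention", and a reader might conclude that 10 points is shown to be too optimistic. The article does not say whether that 7% is absolute or relative, so it cannot carry that conclusion and is not used here.

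**Conclusion.** The power statement is wrong as written for the analysis that answers the aim. For a true reduction of 10 points, DID power is about 24–36% if 392 covers both waves and about 42–62% if it is per wave; within each range, the risk-difference scale gives the lower part and the ratio scales the upper. This rests on equal cells, independent women in each wave, 18% in every untreated cell, and the plan's own 8%, design effect and non-response.

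Two stronger readings are not supported. One is that power is known to be about a quarter, which would need the article to say that 392 spans both waves. The other is that the study plans to report a non-significant result as proof that the training does not work. The article says no such thing and commits to 95% confidence intervals. The risk of that misreading comes from the 80% claim combined with a P-value threshold.

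**What to change.** - Replace the power statement with one for the arm-by-period contrast, on the scale on which it will be tested.
- State whether 392 is per wave or over both waves, and print the resulting DID power at 10 points. Print the difference detectable at 80% where one exists; at 98 per cell on the risk-difference scale there is none, and the text should say so.
- Replace the cumulative stopping rule with target numbers of completed post-delivery interviews for each arm and wave, within the planned three-month windows.
- State that a non-significant DID will be interpreted through its confidence interval and not as absence of effect.

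The changes are mainly wording. They do not oblige the study to recruit more women. The price is a much less favourable stated power, and cell targets may prove hard to fill within the fixed windows, so the text should say what happens if a cell falls short.
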